### Blinding

Case management intervention participants will be fully aware of their group assignment when we ask them to contact our case managers. Participants in the control group will not learn their group assignment until we ask them to complete the questionnaires to collect tertiary outcomes data. Primary and secondary outcomes data are generated by the data department of the pension insurance agency without knowledge of group assignment. The principal investigator and data analysts will be aware of group assignments when analyzing the data. Unblinding of the control group before assessing tertiary outcomes data is not intended.

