### Allocation

The principal investigator (MB) generates random numbers using Stata 16.0 to split both random samples of people with a risk index score of at least 60 points (one in 2021 and one in 2022) into the intervention or control group. Allocation is concealed from the case managers, who are not aware of group assignments until participants contact them. Sample selection and random assignment by the principal investigator uses a data set with pseudonyms. This data set is provided by the German Pension Insurance North electronically. After randomization, the principal investigator transmits the pseudonyms and group assignment also electronically to the German Pension Insurance North. Only the pension insurance agency can link pseudonyms to actual individuals to inform them about the intervention, to collect primary and secondary outcomes from administrative records and to contact participants to send them questionnaires to gather tertiary outcomes. Enrollment for the nested observational study is done by the case managers.

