### Data collection

Outcomes are collected using administrative data from the German Pension Insurance North, patient questionnaires and computerized documentation by case managers (Tables 2 and 3). The administrative data capture our primary and secondary outcomes of the randomized controlled trial completely, reliably, and validly for both the intervention and control group participants. These data are transmitted electronically, encrypted and pseudonymized by the German Pension Insurance North to the University of Lübeck. The patient questionnaire to assess tertiary outcomes of the randomized controlled trial will be sent out 12 months after random assignment by the German Pension Insurance North with a return envelope addressed to the University of Lübeck. The questionnaires of the observational study are handed out to the participants by the case managers and returned to them completed or handed out together with a return envelope addressed to the University of Lübeck. The computerized case manager documentation was developed with the case managers to ensure the feasibility of the documentation, and all case managers were trained on the required documentation before the randomized controlled trials began. Case managers send their computerized documentation of the telephone counseling, the one-on-one interview, and the case management intervention weekly to the researchers, who check it for completeness and validity. The patient forms and computerized documentation of the case managers were tested in a previous pilot study. If participants withdraw their consent, the collected data will be deleted.

The use of administrative data will ensure complete coverage of primary and secondary outcomes from all study participants. Moreover, we created a website to transparently inform study participants about the study and to maintain interest in the study. Three weeks after the first mailing of the 12-month follow-up questionnaire a single reminder is sent, again containing the questionnaire and the return envelope addressed to the University of Lübeck.

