### Data management

A comprehensive data protection concept was developed with the data protection officer of the German Pension Insurance North and clarifies the data processing, rights of participating persons, and technical and organizational measures to ensure the secure and confidential collection, processing, and storage of data. Administrative data are provided by the German Pension Insurance North. Personal data is removed, replaced with the unique study identifier, and submitted to the principal investigator. Questionnaire data are entered, reviewed and exported to statistical software packages for further analysis. Data input and data verification are performed by trained research assistants. The administrative and questionnaire data will be linked using a unique study identifier. Access to the data is limited to the authors and research assistants on the research team, and data management is performed by the authors.

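### The person who generates the allocation also receives the outcome data, and all analysts know the arm, so derivation and modelling choices at the university are unmasked without need

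*Protocol article*

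**What the plan says.** All references are to the protocol article.

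- **Allocation.** The principal investigator "generates random numbers using Stata 16.0 to split both random samples of people with a risk index score of at least 60 points". The same person also draws the sample: "Sample selection and random assignment by the principal investigator uses a data set with pseudonyms". The resulting list then goes to the insurer: "After randomization, the principal investigator transmits the pseudonyms and group assignment also electronically to the German Pension Insurance North".
- **Blinding, outcome generation.** "Primary and secondary outcomes data are generated by the data department of the pension insurance agency without knowledge of group assignment".
- **Blinding, analysis.** "The principal investigator and data analysts will be aware of group assignments when analyzing the data".
- **Data collection.** On the administrative outcome data: "These data are transmitted electronically, encrypted and pseudonymized by the German Pension Insurance North to the University of Lübeck".
- **Data management.** "Personal data is removed, replaced with the unique study identifier, and submitted to the principal investigator". This section also restricts data access to the authors and their research assistants and leaves data management to the authors. No separate analyst is described.
- **Statistical methods.** Cox regression is planned for the primary outcome and for disability pension, and baseline-adjusted Poisson regression for the continuous secondary outcomes. Everyone is analysed as randomised, and there is no interim analysis.

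**The concern.** Intervention participants and case managers cannot be masked in this design. Derivation of the analysis variables and fitting of the models can be, and the protocol expressly gives up masking there for every analyst. One of those analysts made the list that links pseudonym to arm.

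The article shows where discretion could enter after the data arrive:

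- The Objectives speak of applying for rehabilitation, the Sample size section of claiming it, and the Outcomes section of using it.
- Table 2 lists the primary outcome as binary, but a Cox model also needs an event date.
- Employment and benefit data come as days per month and have to be combined before a Poisson model is fitted.

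If such choices are still open when the data arrive, they are made with the arm visible. What is at stake is freedom from analyst influence in the primary and secondary results. Sample size, alpha and power are not affected.

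**Working it through.** **1. Who knows the arm at each step**

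| Step | Who | Arm known? | Section |
|---|---|---|---|
| Sample drawn, allocation generated | Principal investigator | Yes, creates the list | Allocation |
| List sent to the insurer | Principal investigator to insurer | Yes | Allocation |
| Primary and secondary outcomes generated | Insurer's data department | No | Blinding |
| Outcome data received | Principal investigator | Not masked | Data collection; Data management |
| Analysis | Principal investigator and all analysts | Yes | Blinding |

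Masking exists at the insurer and ends at the university. Only derivation and modelling done after the transfer are exposed.

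**2. Do the pseudonyms mask the arm?** They hide identity. The principal investigator assigned the arms to pseudonyms, so any file carrying the same pseudonym, or an identifier linkable to it, can be unmasked by that person. The article does not say whether the study identifier is that pseudonym.

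**3. A sense of scale.** The plan gives no figure on masking. The only usable inputs are those under Sample size: 4500 per arm, 10% against 12%, two-sided 5%. (For 80% power at these rates the usual two-proportion formula gives 3841 per arm, and 4500 per arm gives about 85.8% power. The stated number is therefore not reproduced but is conservative, and this does not bear on the present point.)

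- Expected events: 4500 × 0.10 = 450 and 4500 × 0.12 = 540. The total is 990 and the difference 90.
- Significance boundary near 11%: SE = √(2 × 0.11 × 0.89 / 4500) = 0.0066. Then 1.96 × SE = 0.0129, and 0.0129 × 4500 ≈ 58 events.
- Net shift that would lose the expected effect: 90 − 58 = 32 events, or 32/990 = 3.2%.
- Net shift that would create significance with 10% in both arms: SE = √(2 × 0.10 × 0.90 / 4500) = 0.00632. Then 1.96 × SE = 0.0124, and 0.0124 × 4500 ≈ 56 events, or 56/900 = 6.2%.

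These are unadjusted comparisons of proportions, not the planned Cox model. A coding rule applied to the whole file acts on both arms, so only its net between-arm effect counts towards 32 or 56. Nothing in the article indicates how large that net effect could be.

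**The case against.** The strongest reply is that this is an openly stated choice, not a contradiction. Unmasked analysis of objective administrative data by intention-to-treat is a legitimate pragmatic design. The outcomes are generated blind, and an analysis plan that is not shown may fix the coding rules before any data arrive. Generating the allocation adds no selection risk either, because each yearly sample is drawn on pseudonyms and then split at once. All of this stands and keeps the point minor. It does not remove the point, because the Blinding section is an explicit rule on who knows the arm and not a detail left for later.

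A reader might go further in four ways that the article does not support:

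- *That the existing pseudonymised flow already permits masked analysis at almost no cost.* Pseudonyms do not hide the arm from the person who made the list. A step must be added, and the article gives no cost.
- *That the events are few.* The plan expects 990.
- *That recoding about 3% of records shows a likely bias.* The 32-event margin is what would lose a true effect. The usual fear is a false positive, which needs about 56 net events. No plausible amount of differential recoding is shown.
- *That the insurer merely exports raw records and all coding is done unmasked.* The article says the outcome data themselves are generated without knowledge of group. How much derivation remains for the university is not stated.

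Masking would also be imperfect. Under Recruitment, the university already holds age, gender, nationality, income and benefit durations per pseudonym. The baseline values needed for the adjusted models could be matched back to the allocation list.

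**Conclusion.** The point holds in a limited form. One person draws the sample, creates the allocation list and receives the outcome data. That person and all other analysts know the arms at analysis. Masked outcome generation, complete administrative data and intention-to-treat analysis confine the remaining risk to derivation and modelling choices made after transfer. The size of that risk cannot be derived from the article. The margins of about 32 and 56 net events describe how sensitive the result is and are not an estimate of bias.

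The conclusion assumes that some derivation takes place at the university and that the rules for it are not already locked in a document that is not shown. If they are, little is left beyond saying so. The point is a worthwhile improvement and does not threaten the trial's validity.

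**What to change.** Amend the Blinding section so that, for the administrative primary and secondary outcomes:

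1. the outcome file is kept without the arm variable, or is delivered with arms coded A/B under new identifiers issued by the insurer, which holds the link to individuals;
2. all outcome variables are derived, and the code for the primary and secondary models is locked, on that file;
3. only then is the arm key merged and the locked code run;
4. case-management documentation and observational questionnaires, which exist only for intervention participants and so reveal the arm, stay unlinked until that point.

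The cost is one extra data-handling step and a short delay. If new identifiers are used, they must also be reconciled with the study identifier that links administrative and questionnaire data. The arrangement is not tamper-proof, because the principal investigator holds the allocation list and the baseline data. Where an existing team member without the list can carry out steps 1 and 2, that is preferable. The article reports recruitment as ongoing, with a second sample due in 2022 and outcome data one year after allocation, so at that stage the change could still be made before the outcomes were complete. The number randomised, alpha and power stay as planned.

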### Data collection

Outcomes are collected using administrative data from the German Pension Insurance North, patient questionnaires and computerized documentation by case managers (Tables 2 and 3). The administrative data capture our primary and secondary outcomes of the randomized controlled trial completely, reliably, and validly for both the intervention and control group participants. These data are transmitted electronically, encrypted and pseudonymized by the German Pension Insurance North to the University of Lübeck. The patient questionnaire to assess tertiary outcomes of the randomized controlled trial will be sent out 12 months after random assignment by the German Pension Insurance North with a return envelope addressed to the University of Lübeck. The questionnaires of the observational study are handed out to the participants by the case managers and returned to them completed or handed out together with a return envelope addressed to the University of Lübeck. The computerized case manager documentation was developed with the case managers to ensure the feasibility of the documentation, and all case managers were trained on the required documentation before the randomized controlled trials began. Case managers send their computerized documentation of the telephone counseling, the one-on-one interview, and the case management intervention weekly to the researchers, who check it for completeness and validity. The patient forms and computerized documentation of the case managers were tested in a previous pilot study. If participants withdraw their consent, the collected data will be deleted.

The use of administrative data will ensure complete coverage of primary and secondary outcomes from all study participants. Moreover, we created a website to transparently inform study participants about the study and to maintain interest in the study. Three weeks after the first mailing of the 12-month follow-up questionnaire a single reminder is sent, again containing the questionnaire and the return envelope addressed to the University of Lübeck.

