### Objectives

We designed a randomized controlled trial to clarify if our strategy increases the likelihood to apply for rehabilitation services and improves several secondary and tertiary outcomes compared to the usual approach, where people with chronic diseases and disabilities have to coordinate their services themselves. An observational study was nested to assess how well the case management intervention is implemented.

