## Methods

### Study setting

Our intervention is implemented in 206 postal code districts in the German states of Schleswig-Holstein and Mecklenburg-Vorpommern and overseen by seven regional case managers. Outreach contacts usually take place in the home environment of the participants.

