What (materials)	Personalized letters	Guideline for initial telephone contact and computerized documentation	Guideline for initial one-on-one interview; computerized documentation; questionnaire for the collection of medical data to check eligibility; study information; informed consent form (in duplicate); baseline questionnaire	Worksheet “Analysis of needs and agreement on objectives”; computerized documentation; toolbox with working materials on medical and vocational rehabilitation, rehabilitation aftercare, reintegration and job retention (graded return-to-work, company integration management, rights and obligations of the employer, degree of disability, and termination), reorientation and job acquisition (career orientation, job application training), health and therapeutic services, social security and support; follow-up questionnaire at the end of the case management intervention
What (procedures)	The selection of the persons to be contacted is made using a computerized algorithm that combines various characteristics stored in the individual accounts at the pension insurance institution (e.g., age and duration of receipt of sickness benefits and unemployment benefits) [6]. We applied weights when combining the various administrative data. Individuals with a risk index score of at least 60 points and who have received sickness benefits in the past year are contacted by the German Pension Insurance North.	The person contacted calls the case manager using the contact details provided in the personalized letter and is informed in a telephone counseling about the goals and implementation of the case management intervention. An initial one-on-one interview is arranged with the case manager.	The person meets with the case manager at an agreed upon location for an initial one-on-one interview.	Case management includes an initial phase of up to three appointments, a phase of individually tailored support and a final evaluation meeting. Intermediate assessment meetings are held at regular intervals to review and, if necessary, update needs and goals. Individualized assistance includes, among other things, consultations on health and social benefits, joint workplace meeting, support in applying for further services, acquisition of potential new employers or internships, coaching on reorientation and job applications, and educational and psychological interventions.

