#### Observational study

*Delivered dose:* As part of the observational study, case managers document the intervention components (i.e., telephone counseling, one-on-one interview, and the case management intervention) in a standardized manner using computerized sheets.

*Received dose:* We use the same items assessing knowledge about services supporting participation as in the randomized controlled trial also in the observational study. In addition, we ask which of these services were initiated. Furthermore, the participants rate five statements about how individual needs and goals were identified, five statements about their relationship with the case manager, three statements about the case manager’s competence, five statements about goal attainment, and nine statements about contents of the case management intervention. Ratings of these statements use a 4-point scale from 0 (do not agree) to 3 (completely agree). Finally, we also ask the participants to rate the different components of our multi-component strategy (e.g., the telephone contact), with grades from 1 (very good) to 5 (insufficient).

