### Statistical methods

We will use Cox regressions to analyze our primary outcome and our time-to-event secondary outcome (i.e., disability pension) and report hazard rate ratios and 95% confidence intervals. Poisson regressions with baseline adjustments will be calculated to estimate incidence rate ratios and 95% confidence intervals in our analysis of our continuous secondary outcomes. We will use linear regressions to analyze our continuous tertiary outcomes. The use of administrative data will ensure that all individuals can be included in our analysis as randomized (intention-to-treat).

Subgroup analyses examine whether estimates differ for the first and second cohorts of participants. The analysis of our nested cohort study of case management participants only will describe the implementation of the case management intervention and changes during the case management intervention. We will use paired t-tests for continuous outcomes and McNemar tests for binary outcomes when analyzing the change between the start and end of the case management intervention.

Analyses of our primary and secondary outcomes will not be affected by non-responses or patient withdrawals due to the use of administrative data, but tertiary outcomes may be missing due to non-response or incomplete response to the 12-month follow-up questionnaire. We will use multiple imputation to augment incomplete responses to the 12-month follow-up questionnaire.

We will not perform interim analyses and did not specify a stopping rule. Statistical test will be regarded as significant if the two-sided p-value of a test is less than 0.05. An up-to-date version of Stata (StataCorp, College Station, Texas, USA) will be used to conduct analyses.

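### End-of-case-management questionnaires that rate the case manager may be handed back openly to that case manager, which leaves these ratings open to favourable response bias

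*Protocol article*

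**What the plan says.** **Return route.** Under Data collection, the protocol article gives two return routes for the observational study's questionnaires: "handed out to the participants by the case managers and returned to them completed or handed out together with a return envelope". The envelope goes to the University of Lübeck. The section gives no rule for which route applies to which form or participant, and does not mention sealing.

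**What is rated.** The Observational study section lists five statements on how needs and goals were identified, "five statements about their relationship with the case manager, three statements about the case manager’s competence", five on goal attainment and nine on content. Agreement is scored from 0 to 3, with higher scores more favourable. Participants also grade the components of the strategy from 1 (best) to 5 (worst). Table 2 places these measures at the end of case management, in the observational study only. Table 1 lists the form among the case management materials: "follow-up questionnaire at the end of the case management intervention".

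**What the ratings are for.** Under Objectives: "An observational study was nested to assess how well the case management intervention is implemented". Under Statistical methods, the analysis of case management participants only "will describe the implementation of the case management intervention and changes during the case management intervention". Study setting says that the intervention is "overseen by seven regional case managers".

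**Contrast.** The 12-month questionnaire of the randomized trial is sent by the pension insurance agency, goes straight back to the university in an addressed envelope, and has one reminder.

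**The concern.** The procedure as written lets the person being rated hand out the rating form and take it back filled in. By then, the participant may have had as many as 50 hours of contact over a year with that person, often at home. A participant who expects the case manager to read the answers has a reason to soften a poor judgement of competence or of the relationship.

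Three features make this matter for the nested study. It has no comparison group in which a favourable shift would cancel out. The delivered dose is recorded by the case managers themselves, so the participant's report is the independent check on it, and open hand-back weakens that independence. The route is also left open and no recording of it is described, so any difference in ratings between the two routes could not be examined afterwards.

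At stake is how a reader may interpret high relationship, competence and goal scores. Under open hand-back, part of a high score could be courtesy.

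**Working it through.** The point concerns a procedure, so the main check sets the relevant sections side by side. The arithmetic only fixes the scope and shows what size of shift would matter.

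**1. Who completes the ratings.** The Recruitment section targets 225 case management participants. The Sample size section gives the steps: 4,500 informed, of whom 12.5% make contact, half of those attend the interview, and 80% of those start.
- 4,500 × 0.125 = 562.5 contacts
- 562.5 × 0.5 = 281.25 interviews
- 281.25 × 0.8 = 225 starts

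The stated 225 is reproduced. With seven case managers, the average is 225 / 7 ≈ 32 participants each.

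**2. What is exposed.** The rating statements number 5 + 5 + 3 + 5 + 9 = 27. Those about the case manager personally number 5 + 3 = 8. The remaining 27 − 8 = 19 concern needs and goals, goal attainment and content. Courtesy could spill over to these 19 and to the component grades, but they are less directly exposed. On the grades, 1 is best, so a favourable shift is downward.

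**3. Is there a stated safeguard?**
- Data collection: hand-back is allowed, with no sealing and no limit to the baseline form.
- Data management: a data protection concept is mentioned in general terms, and data access is confined to the authors and research assistants. Data collection treats case managers as distinct from the researchers. An open form passing through a case manager's hands fits badly with that access rule, and the rule does not withdraw the route.
- Data collection also says that the forms were tested in a pilot. That says nothing about who collects them.

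**4. Size, by assumption only.** The documents give neither the share of forms handed back nor any inflation of the ratings. Let f be the share handed back openly and b the average inflation of those ratings on the 0–3 scale. The shift in the mean is f × b.

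| f | b = 0.1 | b = 0.3 | b = 0.5 |
|---|---|---|---|
| 25% | 0.025 | 0.075 | 0.125 |
| 50% | 0.05 | 0.15 | 0.25 |
| 75% | 0.075 | 0.225 | 0.375 |
| 100% | 0.1 | 0.3 | 0.5 |

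For comparison, the half-width of a 95% confidence interval for a mean rating is 1.96 × SD / √225. It assumes that all 225 respond, and it ignores clustering by case manager.
- SD 0.6 (assumed): 1.96 × 0.6 / 15 = 0.078
- SD 0.9 (assumed): 1.96 × 0.9 / 15 = 0.118

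A moderate shift, such as 0.15 (half the forms, inflated by 0.3), would exceed sampling error. A small one, such as 0.025, would not. The calculation shows that the bias could matter. It does not show that it does.

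**5. Start-to-end comparisons.** Table 2 has information about services and work participation at baseline and again at the end of case management. Statistical methods plans paired t-tests and McNemar tests for change. A remedy that altered the return method for the end form alone would introduce a change of collection method into those comparisons.

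**The case against.** **The article is condensed, and a safeguard may exist elsewhere.** The data protection concept could require sealed return, and the two routes might match the two forms, with the baseline form handed back at the interview and the end form posted. Both are possible. However, the article states the hand-back route as procedure, without either limit, so this is more than an omitted detail. If such a rule exists, one clause would settle the matter.

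**A reader might infer that the ratings are in fact biased upward.** The documents do not support that. They give no share by route and no effect size. What stands is that the ratings are open to bias, with favourable as the plausible direction.

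**A reader might infer that all 27 statements are ratings of the case manager.** Only 8 are. Equal exposure of the other 19 is not shown.

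**A reader might infer that the nested study cannot meet its objective.** That goes too far. Implementation is also tracked through standardized computerized documentation of all three contact components, which goes to the researchers weekly for checking. Participants are also asked which services were initiated. The ratings are one strand among several.

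**A reader might infer that case managers will favour hand-back where the relationship is good.** Nothing in the text says so. The open choice of route permits it, no more.

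**Envelope-only return has costs.** This objection stands. Posting may lose some forms, possibly from dissatisfied participants, and the only reminder described is for the 12-month questionnaire. The remedy should therefore not rely on a reminder.

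**Conclusion.** The point holds in a limited form. As written, the plan allows forms rating the case manager to be returned openly to that case manager. The participant ratings, most directly the 8 relationship and competence statements, are therefore open to favourable response bias of unknown size, in a targeted 225 participants without a comparator. The conclusion rests on the article's wording and on the assumption that some participants answer more kindly when the rated person may read the form. The 0.025 to 0.5 point range of possible shifts rests wholly on assumed inputs.

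The randomized comparison is untouched: primary and secondary outcomes come from administrative records, and the trial's 12-month questionnaire goes straight to the university. The case managers' documentation is not affected either. The change is worth making because the ratings serve a stated objective and the safer route is already in use.

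**What to change.** In Data collection, replace open hand-back with return in the envelope addressed to the University of Lübeck, either posted by the participant or sealed by the participant before being given to the case manager. Apply this to the end form, and preferably also to the baseline form so that start-to-end comparisons use one collection method. Tell participants in the cover text that the case manager does not see their answers.

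For forms already returned openly, record the route where it is known and report the Observational study ratings by route. This is a descriptive check only: the route was not randomized, so a difference between routes could reflect who used them.

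The cost is about one sentence in the procedure and a line in the cover text, and the envelopes already exist. The downside is a possibly slightly lower return rate for posted forms, which the sealed hand-over option limits without needing a reminder. Recruitment was still under way at publication and a second sample was due in 2022, so later forms could still benefit.
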